#### Secondary endpoints

The study will also provide a preliminary evaluation of the safety of PSV + sigh by comparing the incidence of the following adverse events in the two study groups: hemodynamic instability with hypotension (i.e., SBP < 90 mmHg) despite vasoactive drugs; arrhythmias with heart rate < 40 or > 140 bpm; radiographic evidence of barotrauma (i.e., pneumothorax, pneumomediastinum, pneumatocoele or subcutaneous emphysema or new chest tube placement.

Furthermore, it will quantify the prevalence of short-term (i.e., within 30 min) and long-term (i.e., within 24 h in the PSV + sigh group) sigh responders defined by improved oxygenation. Finally, it will assess the following clinical outcomes: 28-day mortality; ventilator-free days; PSV level, PEEP value and oxygenation index on day 1–3; number of days on assisted ventilation until day 28; use of rescue treatments; number of quadrants involved on chest x-ray on day 1–5; ICU and hospital length of stay and tracheostomies. The listed variables will be analyzed by comparing the two study groups considering, first, the whole study population and, then, only patients who improved oxygenation during the pre-randomization sigh test (sigh responders).

### Data collection

At enrollment, before the sigh test we will anonymously collect patients’ demographic information (e.g., age, sex, height, weight), past (e.g., hypertension, chronic medications) and recent (e.g., etiology of the acute respiratory failure, days since intubation) medical history, severity of lung injury (e.g., ventilation setting, arterial blood gases, respiratory system compliance, diagnosis of acute respiratory distress syndrome (ARDS)) and of systemic involvement (e.g., presence of shock, number of organ failures) and finally, ventilation data (e.g., RR, Vt, PEEP, FiO_2_, PSV level).

In both groups, for the first 24 h, we will assess the SpO_2_/FiO_2_ ratio, RR and PSV tidal volume every 4 h to further characterize physiologic response to sigh over time.

From day 1 (i.e., within 24 h from randomization) to day 28 or death or discharge from the ICU, the following data will be collected every day between 6:00 and 10:00 in the morning: arterial SpO_2_, arterial and central venous blood gas analyses, ventilation settings and pattern (i.e., sigh pressure level, sigh tidal volume, PSV level, PSV tidal volume, respiratory rate, PEEP, FiO_2_, minute ventilation, P0.1, mean airway pressure), heart rate, arterial blood pressure, central venous pressure, cumulative fluid balance, patient’s comfort assessed using a visual analog scale (VAS), RASS value, SOFA score and dosage of sedative agents and vaso-active drugs.

Moreover, each day we will collect information on use of rescue treatments (i.e., recruitment manoeuvers, use of PEEP ≥ 15 cmH_2_O, prone positioning, inhaled nitric oxide, extracorporeal membrane oxygenation), tracheostomy, switch from the allocated treatment to the other study arm for ≥ 24 h, switch to controlled ventilation for ≥ 24 h, reason for switch to controlled ventilation, adverse events (i.e., hemodynamic instability with hypotension with SBP < 90 mmHg despite vasoactive drugs; arrhythmias; radiographic evidence of barotrauma with pneumothorax, pneumomediastinum, pneumatocoele, or subcutaneous emphysema), SBT performance and reason for SBT failure, extubation or separation from mechanical ventilation, reintubation and reason for reintubation with time. We will collect data on day 28 for all enrolled patients on mortality, extubation that occurred outside the ICU and readmission to ICU.

### Sample size

The sample size was computed based on the hypothesis that PSV + sigh might decrease the rate of failure of assisted ventilation compared to standard PSV. Based on previous data [21], the expected proportion of failure in patients undergoing PSV will be 22% and we hypothesized a proportion of 15% for patients in the PSV + sigh group. Assuming non-inferiority of PSV + sigh treatment, with a tolerance of 5% we estimated that a sample size of 258 patients (with 129 patients per study arm) will be sufficient to assess feasibility of the PSV + sigh strategy in this pilot phase with power of 0.8 and alpha 0.05.

### Statistical analysis

Continuous normally distributed variables will be expressed by their mean and standard deviation or as medians and their interquartile ranges when not normally distributed. Categorical variables will be expressed as number and proportion (%). To assess the feasibility of PSV + sigh as compared to PSV (i.e., the primary endpoint), we will compute the proportion of patients experiencing at least one of the following events in each arm: switch to controlled ventilation for ≥ 24 h consecutively; use of PEEP ≥ 15 cmH2O, prone positioning, inhaled nitric oxide, extracorporeal membrane oxygenation or reintubation within 48 h from extubation.

We will compare the two proportions using the one-tailed non-inferiority test for proportions with a 5% tolerance. We will use 0.05 as the significance level. The same method will be adopted to evaluate the safety of PSV + sigh, which is a secondary endpoint. Prevalence of sigh responders in the two arms will be compared using the chi-squared or Fisher’s exact test. Ventilator-free days will be calculated as the difference between the duration of follow up (up to 28 days) and the number of days of intubation before successful extubation or separation from mechanical ventilation for tracheostomized patients. For all the secondary endpoints, we will use the chi-squared or Fisher’s exact test in the case of binary variables or the *t* test or Wilcoxon signed rank test for continuous variables. Time to death or extubation will be analyzed using Kaplan-Meier survival curves. Adjustement for potential confounding factors will be evaluated using appropriated regression models.

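### Safety is given two incompatible tests, one of them a 5-point non-inferiority test that 129 patients per arm can pass reliably only when the event is rare

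*Protocol article*

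**What the plan says.** For the primary endpoint, the Statistical analysis section states: "We will compare the two proportions using the one-tailed non-inferiority test for proportions with a 5% tolerance", and then "We will use 0.05 as the significance level". The next sentence extends this to harms: "The same method will be adopted to evaluate the safety of PSV + sigh, which is a secondary endpoint". No separate margin, expected rate or power is given for safety.

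Three sentences further on, in the same paragraph, another rule begins: "For all the secondary endpoints, we will use the chi-squared". It prescribes chi-squared or Fisher exact tests for every binary secondary endpoint and makes no exception for safety.

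The Secondary endpoints section introduces the harms as follows: "The study will also provide a preliminary evaluation of the safety of PSV + sigh by comparing the incidence of the following adverse events". They are hypotension not corrected by vasoactive drugs, arrhythmias outside set heart-rate limits, and radiographic barotrauma. All are binary. The article does not say whether each is tested separately or whether they are pooled.

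The Sample size section assumes 22% failure on PSV and 15% on PSV + sigh, with a 5% tolerance. It arrives at 258 patients, "with 129 patients per study arm", "with power of 0.8 and alpha 0.05".

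**The concern.** There are two problems.

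**Two tests for one question.** A non-inferiority test takes an excess of 5 points or more as its null hypothesis, and rejecting that null is a positive statement about safety. A chi-squared or Fisher test takes equality as its null, and failing to reject it establishes nothing. An analyst following the article could report either.

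**A borrowed margin.** The 5-point absolute tolerance was set for an endpoint expected in 22% of control patients, and the sample size relies on an expected benefit. Neither condition is stated for the harms. Whether the test passes then depends largely on the base rate of the event, which the article does not give. A fairly common event would usually fail with no excess at all, while a sufficiently rare one could pass despite a real relative increase.

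The Discussion says that no randomised trial has yet tested the long-term safety of sigh, so a formal verdict from this trial could be given more weight than it can bear.

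**Working it through.** **Inputs from the article.** n = 129 per arm; margin 0.05; one-sided alpha 0.05 (z = 1.645); power 0.80 (z = 0.842); primary rates 0.22 and 0.15. Adverse event rates are not given, so those below are assumptions, shown over a range.

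**Step 1: reproduce the planned sample size.** Failure is a harm, so the distance from the null is the margin plus the assumed benefit: 0.05 + 0.07 = 0.12.

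n = (0.22 × 0.78 + 0.15 × 0.85) × (1.645 + 0.842)² / 0.12² = 0.2991 × 6.18 / 0.0144 ≈ 128.4, rounded up to 129.

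The stated figure reproduces, and power at 129 is 80.2%. Of the 12 points of distance, 7 come from the assumed benefit.

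**Step 2: remove the benefit.** With equal true rates p, the normal approximation to the chance of passing is Φ(0.05/SE − 1.645), where SE = √(2p(1 − p)/129).

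- p = 0.22: SE = 0.0516; 0.05/0.0516 − 1.645 = −0.68; chance 25%.
- p = 0.10: SE = 0.0374; 0.05/0.0374 − 1.645 = −0.31; chance 38%.

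Exact binomial enumeration at 129 per arm gives the following. Wald means the unpooled standard error; score means the Farrington-Manning test.

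| True rate, both arms | Passes (Wald) | Passes (score) |
|---|---|---|
| 5% | 60% | 54% |
| 10% | 38% | 37% |
| 20% | 27% | 26% |
| 22% | 25% | 25% |
| 30% | 23% | 22% |

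Under Wald, the chance falls below 50% once the rate exceeds about 7%. For an 80% chance of passing with no excess, n per arm = 2p(1 − p) × 6.18 / 0.05². This is 446 at 10%, 792 at 20% and 1039 at 30%.

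**Step 3: rare harms with a real excess.** Same enumeration, each event tested separately:

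| Control vs sigh | Relative increase | Passes (Wald) | Passes (score) |
|---|---|---|---|
| 1% vs 2% | doubled | 80% | 70% |
| 1.5% vs 3% | doubled | 60% | 50% |
| 2% vs 4% | doubled | 43% | 34% |
| 3% vs 6% | doubled | 22% | 17% |
| 1% vs 3% | tripled | 54% | 43% |
| 1.5% vs 4.5% | tripled | 28% | 20% |
| 2% vs 6% | tripled | 14% | 9% |

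**Step 4: one data set, two readings.** Suppose 3/129 on sigh and 1/129 on PSV. The difference is 2/129 = 1.55 points, SE = √[(0.0227 + 0.0077)/129] = 0.01535, and the one-sided 95% upper bound is 1.55 + 1.645 × 1.535 = 4.1 points. This is below 5, so the carried-over rule declares non-inferiority. The chi-squared/Fisher rule finds only no significant difference. The same four events yield a positive statement under one sentence and none under the other.

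**The case against.** The strongest replies are these.

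- **Safety is called preliminary, and power is claimed only for feasibility.** Low power for a secondary endpoint in a pilot is ordinary, and failing to show non-inferiority is the cautious error. This stands: the low pass rates for common events do not create false reassurance. They do show that a formal test adds little.
- **The rare-harm examples that pass often have a true excess of only 1 to 2 points, inside the tolerance.** Passing them is what the test is designed to do. This stands too. The complaint is that the margin is unjustified for harms, not that the test malfunctions.
- **The unit of testing and the exact test statistic are unstated.** If harms are pooled into a more frequent outcome, the rare-harm argument largely drops out and only the power argument remains. The score test also gives lower pass rates than Wald for rare events, which is why both are shown.
- **The test is not the only safeguard.** Under Study organization, all adverse events are monitored by and reported to the coordinating centre.

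A reader might infer that the test would often wave through a doubling or tripling of barotrauma. The article does not support that. It gives no barotrauma rate and does not specify per-event testing. A doubling passes often only at control rates up to about 1.5% to 2%, and a tripling only at about 1% or below. Nor does it say that a safety verdict will be carried into the larger trial; the Discussion makes that trial depend on a positive result without mentioning one.

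None of this removes the conflict between the two sentences, which needs no assumed rate. It is stated text, so a separate analysis plan would have to correct it rather than merely add detail.

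**Conclusion.** The point holds in a limited form and should be acted on.

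- **Certain from the text:** the article prescribes two tests with different null hypotheses for safety, and it carries over the 5-point margin without justification.
- **Following from the plan's own figures:** without the assumed 7-point benefit, the chance of passing at the plan's own 22% rate falls from 80% to 25%.
- **Conditional on assumed rates:** events above about 7% fail more often than not with no excess. A real multiple-fold excess can pass if events are tested separately and the control rate is about 1% to 2% or less; above that it seldom does.

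The planned 129 per arm is not in dispute for the primary endpoint. It would be wrong to conclude that the sample size is miscalculated or that the trial is set up to conceal harm. The conclusion is only that a pass or fail on safety would reflect the unstated base rate more than the effect of sigh.

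**What to change.** In the Statistical analysis section, remove the sentence that applies the 5-point non-inferiority test to safety. In its place, state that each adverse event will be reported by arm as counts, with a risk difference and an exact or score 95% confidence interval, and that no non-inferiority or safety claim will be made from this pilot. Amend the chi-squared/Fisher sentence to agree, for example by excepting the adverse events from it.

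A separately justified margin for each harm would also answer the objection to the margin, but it would need expected rates that the article does not give, and 129 per arm would still be too few for common events.

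The change touches two sentences and leaves design, sample size and data collection as they are. The price is a formal safety verdict, which this trial could not have supported. Estimates with intervals also suit an evaluation that the article itself describes as preliminary.

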### Sigh test

To explore the possibility of implementing predictive enrichment in a larger future RCT [17], we planned a pre-randomization test to assess the prevalence of patients with AHRF with improved oxygenation after the introduction of sigh. After enrollment, FiO_2_ will be titrated to obtain pulse arterial oxygen saturation (SpO_2_) of 90–96% maintaining clinical PSV settings including PEEP; then, all patients will undergo a clinical test of PSV + sigh to assess the prevalence of improved oxygenation in sigh responders vs. non-responders. To this end, we will first record the SpO_2_/FiO_2_ ratio at the start of the test; then, 30 min after the introduction of sigh as the cyclic pressure control phase set at 30 cmH_2_O for 3 s once per minute [14], SpO_2_/FiO_2_ will be collected again to quantify the number of patients in whom this ratio increased (i.e., “sigh responders”) [18]. To deliver sigh, ventilators will be switched to biphasic positive airway pressure mode with the lower pressure-level set at clinical PEEP and the higher pressure-level of the sigh set at 30 cmH_2_O with a 3-s inspiratory time and then a 57-s expiratory time [16].

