### Randomization

At the end of the sigh test, patients will be randomized through an online automatic centralized and computerized system to one of the two study groups (1:1 ratio): PSV or PSV + sigh. Due to the nature of the intervention, blinding will not be feasible.

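### The between-arm test of sigh responders either tests a baseline variable or has no comparator, and a responders-only analysis cannot show whether response modifies the effect of sigh

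*Protocol article*

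**What the plan says.** All references are to the Protocol article.

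- **Sigh test.** The motive is stated as "To explore the possibility of implementing predictive enrichment in a larger future RCT", and the immediate purpose follows: "we planned a pre-randomization test to assess the prevalence of patients with AHRF with improved oxygenation after the introduction of sigh". Every enrolled patient has the test. A responder is a patient whose SpO2/FiO2 is higher after 30 minutes of sigh than at the start.
- **Randomization.** "At the end of the sigh test, patients will be randomized", 1:1.
- **Secondary endpoints.** The trial will quantify "short-term (i.e., within 30 min) and long-term (i.e., within 24 h in the PSV + sigh group) sigh responders defined by improved oxygenation". The listed outcomes are compared between arms twice, first in everyone and then in "only patients who improved oxygenation during the pre-randomization sigh test (sigh responders").
- **Statistical analysis.** "Prevalence of sigh responders in the two arms will be compared" with a chi-squared or Fisher's exact test. Regression is mentioned only for adjustment for confounders.
- **Data collection.** SpO2/FiO2 is recorded every 4 hours over the first 24 hours in both groups, "to further characterize physiologic response to sigh over time".

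**The concern.** The article gives two definitions of a responder, and the stated arm comparison suits neither. Short-term status is fixed before allocation, so allocation cannot affect it. Long-term status exists in one arm only, so no two-arm table can be formed. Patients recovering from acute respiratory failure may improve over 24 hours without sigh, and a one-arm prevalence cannot tell that improvement, or measurement noise, from an effect of sigh.

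The outcome analysis has a separate weakness. Predictive enrichment depends on effect modification: does sigh help responders more than non-responders? A result in responders alone looks the same whether sigh helps only them or helps everyone. The composite failure endpoint is also outside the responder analysis, because that analysis covers the variables listed as secondary endpoints. At stake is how much this pilot can tell the designers of a later trial about enrichment.

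**Working it through.** **1. The plan's own figure.** The article gives no figure for the responder analyses, so the check starts from the sample size. Inputs (Sample size, Statistical analysis): failure 22% vs 15%, tolerance 5 points, one-tailed alpha 0.05, power 0.80.

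n per arm = (1.645 + 0.842)² × (0.22×0.78 + 0.15×0.85) / (0.05 + 0.07)² = 6.18 × 0.2991 / 0.0144 ≈ 128.4, so 129. This matches the stated 129 per arm (258 in total), which is used below.

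**2. Short-term response between arms.** The order is test, then randomisation. Both arms are random samples from one population, so equal prevalence is true by design. Simulating 129 per arm with a two-sided 5% test, 50,000 trials each, gave rejection rates of 5.0%, 5.4% and 5.1% at prevalence 30%, 50% and 70%. The prevalences are assumptions, as the article gives none. The test returns its error rate and nothing about sigh.

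What can be estimated is the pooled prevalence. Its 95% half-width is 1.96 × √(π(1−π)/258), which is 5.6, 6.1 and 5.6 points at π = 30%, 50% and 70%.

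**3. Long-term response between arms.** Secondary endpoints defines "long-term (i.e., within 24 h in the PSV + sigh group) sigh responders defined by improved oxygenation". Statistical analysis compares prevalence in two arms. Read together, the PSV column of the table is undefined. Data collection shows that the readings needed to fill it will exist.

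**4. What responders alone can show.** Take two truths on the failure endpoint: a 7-point benefit in everyone, or 7 points in responders and 0 in non-responders. With responder prevalence π, the second gives 7π points overall.

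| | Responders | Non-responders | Whole population (π = 30 / 50 / 70%) |
|---|---|---|---|
| Benefit in everyone | 7 | 7 | 7 / 7 / 7 |
| Benefit in responders only | 7 | 0 | 2.1 / 3.5 / 4.9 |

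The responder column is the same in both rows. The non-responder column separates them, and the article does not plan to report it.

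The responder comparison is also weak in itself. For 22% vs 15%, two-sided 5%, power = Φ[(0.07 − 1.96·SE₀)/SE₁], with SE₀ = √(2×0.185×0.815/129π) and SE₁ = √(0.2991/129π). This gives about 12%, 17% and 23% at π = 30%, 50% and 70%.

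**5. Precision of an interaction.** The interaction is the risk difference in responders minus that in non-responders. With p the PSV + sigh failure rate in responders, and 22% in the other three cells:

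SE² = [0.22×0.78 + p(1−p)]/(129π) + 2×0.22×0.78/[129(1−π)]

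Case A puts the whole overall 7-point benefit in responders, so their difference is 7/π points. At π = 30% that is 23.3, capped at the 22% control rate. Case B is 7 points in responders and 0 in non-responders.

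| π | A: responder difference | A: 95% half-width | A: power | B: 95% half-width | B: power | B: n per arm for 80% |
|---|---|---|---|---|---|---|
| 30% | 22 | 17.8 | 68% | 21.0 | 10% | 2,383 |
| 50% | 14 | 18.7 | 31% | 19.6 | 11% | 2,058 |
| 70% | 10 | 21.4 | 15% | 21.6 | 10% | 2,517 |

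Example for B at 50%: 64.5 per cell, SE² = 0.2991/64.5 + 0.3432/64.5 = 0.00996, SE = 0.0998, half-width 1.96 × 0.0998 = 19.6 points.

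**The case against.** The other side has substance.

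- **An article condenses.** An absent interaction term could sit in an analysis plan that is not shown, and alone would be no finding. That stands. But the arm comparison of prevalence, the one-arm definition and the restriction to responders are choices the article states.
- **Prevalence is the immediate aim.** That stands too: pooling the arms estimates short-term prevalence adequately. It needs no arm comparison, and comparing outcomes in responders already goes beyond prevalence.
- **Non-responder results follow by subtraction.** True for counts of binary outcomes. No such estimate or interval is planned, and medians or rank tests cannot be subtracted.
- **The 24-hour data cover both groups,** so a two-arm comparison may be intended. Possibly, but then the definition in Secondary endpoints contradicts it and the sections must be reconciled.
- **Failure-related outcomes are partly covered.** Use of rescue treatments is on the secondary list. The composite is not.
- **The pilot cannot settle effect modification.** Correct, and it limits the remedy to an estimate with its interval.

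Two stronger readings are not supported. A reader might infer that the decision to enrich the later trial would rest on the responder comparison. The article speaks only of exploring the possibility, and its Discussion links the larger trial to this pilot's results without mentioning responders. A reader might also infer that most 24-hour responders would be noise. The article gives no variability for SpO2 and does not say whether one reading or several count. Adjusting ventilation settings also allows FiO2 steps of 0.1; going from 0.5 to 0.4 multiplies the ratio by 1.25 at unchanged SpO2. No noise percentage can be defended from this.

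**Conclusion.** The point holds in three parts. The between-arm test of short-term response checks only chance imbalance. Long-term response, as defined, has no comparator. The whole-population and responders-only analyses, confined to secondary endpoints, cannot establish whether responder status modifies the effect of sigh.

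The first two follow from the article's wording and need no assumption. The third follows from the logic of effect modification; its figures assume 30–70% prevalence and the planning failure rates. The damage is limited: prevalence can still be estimated, these analyses are secondary and exploratory, and the primary endpoint, sample size and safety comparison are not affected. It should be corrected because the data for a better analysis will be in hand.

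**What to change.** 1. Replace the between-arm test of short-term response with one pooled prevalence and its 95% CI.
2. Reconcile Secondary endpoints with Statistical analysis: define 24-hour oxygenation improvement at one fixed time, identically in both arms, from the 4-hourly SpO2/FiO2 readings, and compare the arms.
3. For the primary and key secondary endpoints, report the arm effect with CI in responders and in non-responders, plus an arm-by-response interaction estimate with CI from all randomised patients. Label it exploratory and state the expected imprecision. Using the continuous change in SpO2/FiO2 as the modifier is optional.

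The cost is analysis wording. All non-responders are randomised and followed, and the 24-hour readings are already collected in both groups, so no new data or patients are needed.

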**Discussion:**

PROTECTION is a pilot randomized controlled trial testing the feasibility of adding sigh to PSV. If positive, it will provide physicians with an effective addition to standard PSV for lung protection, able to reduce failure of assisted ventilation. PROTECTION will provide the basis for a future larger trial aimed at verifying the impact of PSV + sigh on 28-day survival and ventilator-free days.

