### End of follow up

Enrolled patients will be observed until day 28, ICU discharge or death, whichever comes first.

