## Discussion

PROTECTION is a pilot randomized controlled trial to test the long-term clinical feasibility of the addition of sigh to PSV in comparison to standard PSV. If positive, it will provide the basis for a future larger trial aimed at verifying the impact of PSV + sigh on a composite outcome endpoint including 28-day survival and ventilator-free days. Moreover, it will provide physicians a physiologically sound addition (i.e., sigh) to standard PSV for lung protection able to favor assisted ventilation.

Mortality remains considerably high (around 40%) in intubated patients with AHRF [6]. The clinical severity of lung injury at presentation and early appropriate treatment are the main determinants of patients’ outcomes [19]. However, while the lungs recover, VILI might significantly impact survival [1]. Recent studies testing strategies that enhance lung protection (e.g., early referral to an extracorporeal membrane oxygenation (ECMO) center [22]; use of muscle relaxants during the first 48 h after intubation [23]; early use of extended sessions of prone positioning [24]) yielded significantly decreased mortality. However, such trials enrolled only the most severely ill patients with AHRF on controlled mechanical ventilation. A recent large observational study [6], instead, showed that most ventilated patients admitted to the ICU have mild to moderate AHRF or ARDS that leads to considerably high mortality (≈ 35%) anyway. Moreover, the same study reported that around 30% of invasively ventilated patients with AHRF and ARDS are on some form of spontaneous breathing from day 1 after intubation, independent of the severity of their illness [6], and this proportion likely increases within 1 week. Thus, there is an urgent need for interventions that increase lung protection during assisted ventilation.

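### The stated ventilator-free-day formula uses follow-up that ends at ICU discharge or death, so it can hide a weaning benefit and gives credit for death after extubation

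*Protocol article*

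**What the plan says.** The Statistical analysis section of the protocol article defines VFD as "the difference between the duration of follow up (up to 28 days) and the number of days of intubation before successful extubation", or before separation from the ventilator in tracheostomised patients. The first term is therefore each patient's own follow-up time, capped at 28 days, and not a constant 28. The section gives no rule for patients who die and no starting point for the intubation count.

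The End of follow up section is the only place that defines follow-up: "Enrolled patients will be observed until day 28, ICU discharge or death, whichever comes first". Daily recording, in Data collection, runs over the same span: "to day 28 or death or discharge from the ICU, the following data will be collected every day". The same section adds one later item: "We will collect data on day 28 for all enrolled patients on mortality, extubation that occurred outside the ICU and readmission to ICU".

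VFD stands among the clinical outcomes under Secondary endpoints ("28-day mortality; ventilator-free days; PSV level, PEEP value and oxygenation index on day 1–3"). These are compared between arms in all patients and then in sigh responders. The main Discussion names VFD for the follow-on trial, as part of "a composite outcome endpoint including 28-day survival and ventilator-free days".

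**The concern.** VFD is meant to reward being alive and off the ventilator. That works only if every patient is scored over the same window and death receives the worst score. Here the window is shortened by ICU discharge, which is usually a good event, and by death, which is the worst one, and the formula treats the two alike.

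Two things are at stake. First, the between-arm difference in VFD may say little about weaning, because the score mostly reflects how long patients stay in ICU after extubation. Second, the pilot's VFD estimate is a natural planning input for the larger trial, and it would be on a different scale from the usual 28-day measure.

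**Working it through.** The protocol gives no numerical VFD figure, so there is none to reproduce. The check applies the stated rule to example patients.

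**Inputs.** V = days from randomisation to successful extubation or separation. D = day of ICU discharge. M = day of death. Counting from randomisation is an assumption for V. It matches Data collection, which places day 1 within 24 h of randomisation.

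**Formulas.**
- As written (Statistical analysis with End of follow up): VFD = min(28, D, M) − V.
- Alternative reading, follow-up to day 28 or death: VFD = min(28, M) − V.
- Fixed window: VFD = 28 − V, set to 0 for death by day 28 or if still ventilated at day 28.

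| Example patient | As written | To day 28 or death | Fixed window |
|---|---|---|---|
| Extubated day 5, discharged alive day 10 | 10 − 5 = 5 | 28 − 5 = 23 | 23 |
| Extubated day 5, in ICU on day 28 | 28 − 5 = 23 | 23 | 23 |
| Extubated day 5, discharged alive day 7 | 7 − 5 = 2 | 23 | 23 |
| Extubated day 20, in ICU on day 28 | 28 − 20 = 8 | 8 | 8 |
| Extubated day 5, dies in ICU day 10 | 10 − 5 = 5 | 5 | 0 |
| Extubated day 5, dies in ICU day 20 | 20 − 5 = 15 | 15 | 0 |
| Ventilated until death on day 10 | 10 − 10 = 0 | 0 | 0 |

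**Discharge.** As written, each day of earlier discharge after a given extubation day removes one VFD. A survivor ventilated for 5 days and discharged on day 7 scores 2, below a survivor ventilated for 20 days who is still in ICU on day 28 (8).

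**Effect on a weaning benefit.** Take a control patient extubated on day 9 and discharged on day 12: 12 − 9 = 3.
- Extubation and discharge both three days earlier: 9 − 6 = 3. The benefit vanishes; the fixed window shows 22 against 19.
- Extubation three days earlier and discharge four days earlier: 8 − 6 = 2. The benefit reverses; the fixed window again shows 22 against 19.

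**Average size, illustrative only.** A simulation with all inputs assumed used:
- exponential ventilation times with means of 6 and 9 days in the two arms;
- a mean ICU stay after extubation of 2, 3 or 5 days, the same in both arms;
- 28-day mortality of 15, 25 or 35%, the same in both arms, with death times uniform over 28 days.

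The between-arm difference was 0.1 to 0.3 days as written, against 1.7 to 2.3 days with the fixed window and death scored 0. Across the scenarios the written rule kept between about 4% (0.09/2.25) and 18% (0.31/1.68) of the fixed-window difference. It did not change the sign in any of them.

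**Death.** The credit appears under both readings (5 and 15 in the table). It concerns only deaths after extubation or separation; a patient who dies while ventilated scores 0 in any case.

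**The case against.** The strongest reply is that the discharge penalty rests on one reading of follow-up. The day-28 items in Data collection cover all enrolled patients, and Secondary endpoints lists 28-day mortality and hospital stay. The study therefore does look beyond ICU discharge, and recording extubation outside the ICU chiefly serves ventilation outcomes. This stands in part: on that reading the penalty disappears (23 against 23). But nothing says that these data extend the follow-up used for VFD, and the only section that defines follow-up ends it at ICU discharge. The death credit survives both readings.

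A second reply is that a condensed article leaves such detail to a fuller document. That would excuse silence. Here the article states a formula and a follow-up rule which, applied together, give a wrong score.

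A reader might also infer more than the documents support:
- *That the arm that recovers faster must score worse.* Equal shifts in extubation and discharge leave the score unchanged. Reversal also needs a shorter ICU stay after extubation.
- *That VFD will be negative because patients are enrolled after up to about a week of intubation.* The formula gives no start for the intubation count, and counting on the follow-up clock is the natural reading. The origin should be stated, but negative scores are not what the text prescribes.
- *That the mortality of about 35 to 40% quoted in the Discussion measures the death credit.* That is overall mortality in cited populations. The documents give no rate of death after extubation.

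**Conclusion.** The point holds. Under the document's own definition of follow-up, VFD measures the time from extubation to ICU discharge, death or day 28. It can largely hide a real weaning benefit, and can reverse it if the ICU stay after extubation also shortens. If follow-up is taken to run to day 28, only the death defect remains: a patient extubated on day 5 who dies on day 10 scores 5 instead of 0.

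The example scores follow by arithmetic once days are counted from randomisation. The average loss of contrast (0.1 to 0.3 days against 1.7 to 2.3) rests wholly on assumed inputs and shows scale only. How often death follows extubation in this trial is not known from the documents.

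The point should be corrected before analysis, but it does not threaten the pilot's main conclusion, as a reader might infer from VFD's place in the larger trial. VFD is one of several secondary endpoints. The primary endpoint, its non-inferiority test and the sample size do not use it, and the larger trial can set its own definition.

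**What to change.** Replace the formula with one over a fixed window, for every patient and regardless of ICU discharge:

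- VFD = 28 minus the days of invasive ventilation from randomisation to day 28.
- VFD = 0 for death by day 28, in or out of the ICU, and for anyone still ventilated at day 28.
- A patient discharged alive from the ICU off the ventilator counts as ventilator-free to day 28, unless the day-28 data (mortality, extubation outside the ICU, ICU readmission) show otherwise.
- State that the ventilation count starts at randomisation.

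The End of follow up section should also say that its stopping rule governs daily ICU observation and not the VFD window.

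The cost is mainly wording, since the day-28 items are already planned for all enrolled patients. One gap remains: ventilator days after an ICU readmission are not among those items. A simple scoring rule fixed in advance, or one added item on the case report form, would cover those patients. The Trial status section describes recruitment as still open, so the change can be made before analysis.
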